**Figure 1 F1:**
[figure not shown]
Study flow chart.

### Primary and secondary endpoints

The primary endpoint of the study is the change in depression symptoms (BDI-II total score) during the trial. Secondary endpoints include changes in general psychopathology, sleep, circadian functioning (including melatonin assessment), affective dysregulation, behavior, and attention parameters. All questionnaires will be presented in German, and will be completed within the hospital.

#### Assessments

##### BDI-II

BDI-II is a measure of the severity of depressive symptoms and has been used widely in treatment studies for juvenile depression [41]. It can be used to directly compare effect sizes between different kinds of interventions. The German version has shown good psychometric properties, with good test-retest-reliability (*r* ≥ 0.75) in a non-clinical population, and good internal consistency (α coefficient = 0.92) for adolescent inpatients with depression [48,49].

##### Clinical global impression scale

Assessment of general psychopathology will be performed using the Clinical Global Impression Scale (CGI) for estimating symptom severity (CGI-S) and improvement (CGI-I) [50,51]. The CGI is a 7-point scale that requires a rating of illness severity at the time of assessment. Because severity estimation in the CGI is performed in relation to other patients, it is a subjective assessment tool. In the proposed study, rating will be performed by clinicians blinded to group allocation.

##### Sleep questionnaire B - revised

Sleep and sleep difficulties will be assessed by using the Sleep Questionnaire (Schlaffragebogen) B - Revised (SF B/R) described by Görtelmeyer *et al*. [52]. This questionnaire contains 31 questions, assessing the 2 weeks prior to assessment. Completion takes about 5 to 10 minutes, and 11 sleep indices can be created including: difficulties in sleep onset and in sleeping through the night, premature awakening, general sleep characteristics, total sleep duration, and sleep factors consisting of sleep quality, feeling of recovery after sleeping, mental balance before going to sleep, feeling of mental exhaustion before going to sleep, and psychosomatic symptoms during sleep phase. Internal consistency is moderate to excellent (α coefficient = 0.68 to 0.92) for clinical populations. Test-retest reliability indicates that relatively stable sleep-related behavior and experiences can be assessed (r = 0.53 to r = 0.91).

##### DLMO

Melatonin production by the pineal gland is under the influence of the suprachiasmatic nucleus of the hypothalamus (SCN), which receives information from the retina about daily patterns of light and darkness [53]. Production of melatonin is inhibited by light and induced by darkness. Hence, when dim lighting is provided, the human body starts producing melatonin about 2 hours before bedtime, and this physiological process is called DLMO. Assessment of the DLMO can be considered the gold standard for measuring melatonin levels and circadian rhythms. In the present study, at the assessments T1, T2, and T5, four sequential melatonin saliva samples will be collected at hourly intervals, respectively. Collection starts from 4 hours before predicted bedtime (19.00 to 22.00 hours) under conditions of dim light. Light therapy has been shown to be most effective when it is applied about 7.5 to 9.5 hours after the individual DLMO [22].

Saliva will be sampled using sterile collection devices (Salivettes; Sarstedt AG & Co, Nümbrecht, Germany). On the day of sampling, patients will be instructed to avoid caffeinated beverages, orange juice, eggs, chocolate, and bananas, because all these have been shown to have a possible influence on melatonin level. During the evening, electronic devies such as video games, TV, and cell phones will not be allowed because the light produced by such devices may have a melatonin-suppressing effect [54]. Patients will be instructed to refrain from food or drinks for 30 minutes before sampling, and directly before sampling they will be instructed to rinse their mouth with water. Samples will be stored at −26°C until analysis, and all samples will be analyzed simultaneously. This will be performed in a specified laboratory in which melatonin concentrations will be determined, and the individual DLMO will be calculated.

##### Morningness-eveningness questionnaire

For estimating circadian preferences independent of physiological parameters, the German version of the Morningness-Eveningness Questionnaire (MEQ) will be used [44,55]. With this questionnaire, the individual chronotype can be estimated based upon 19 questions that are summed to give a total score and the individual DLMO is then estimated, as it has been shown to have a good correlation with the MEQ [56]. Using this procedure, the optimal time point for light exposure can be estimated directly (about 7.5 h after the individual DLMO) without the requirement for physiological data.

##### Child behavior checklist

The Child Behavior Checklist (CBCL) is one of the best-studied, empirically derived parent checklists for measuring general child and adolescent psychopathology [57]. It assesses the child’s behavior over the past 6 months using a total of 118 items (plus two optional questions), and is rated by the parents or primary caregivers. The questionnaire includes a total problem score, two higher level scales (externalizing problems and internalizing problems), and eight syndrome scales (withdrawn, somatic complaints, anxious/depressed, social problems, thought problems, attention problems, delinquent behavior, and aggressive behavior). The reliability, factorial validity and discriminant validity of the German adaptation of the CBCL have been confirmed by previous studies [58,59]. Recently, a specific ‘dysregulation profile’ has been identified in the CBCL, capturing severe affective dysregulation (CBCL-DP) [60]. This profile is characterized by simultaneous high values on the syndrome scales ‘anxious/depressed,’ ‘attention problems,’ and aggressive ‘behavior.’ The CBCL-DP has been consistently found to be associated with disruptive behavior disorders, suicidal behavior, and reduced need for sleep [61-64], and it will be calculated to assess the phenotype of affective dysregulation.

##### Strengths and difficulties questionnaire

In addition to the CBCL, the Strengths and Difficulties Questionnaire (SDQ) will be used in order to assess short-term changes and to evaluate parent and patient ratings. The SDQ is a brief behavioral screening questionnaire assessing 25 attributes, some positive and others negative, which can be allocated to five scales (emotional symptoms, conduct problems, hyperactivity/inattention, peer relationship problems, and pro-social behavior) [65]. These scales can be summed to calculate a total difficulties score and, like in the CBCL, a dysregulation profile can be calculated that corresponds to the CBCL-DP, with the advantage of being able to assess short-term changes [66]. In this study, patient and parent rating versions of the SDQ will be used. The sensitivity to change of the SDQ allows estimation of treatment efficacy (α = 0.73; retest stability = 0.62) [67], therebv allowing monitoring of symptom changes of affective dysregulation and behavior during the trial.

##### Tests of attentional performance

With the Tests of Attentional Performance (TAP), a large spectrum of specific attentional performances can be assessed in a computerized form [68]. The following four subtests will be administered to evaluate highly relevant attention-related parameters.

1) Covert shift of attention. This assesses the ability to shift the attentional focus, measuring reaction times for valid and invalid cues in a visual reaction time task.

2) Go/nogo. Assesses the ability to suppress a response in the presence of irrelevant stimuli.

3) Alertness. Assesses the general level of arousal (tonic arousal), its stability over a longer period (intrinsic arousal) and the magnitude of elevation of arousal, induced by a warning signal (phasic arousal).

4) Divided Attention. Assesses the ability to divide attention to auditory and visually presented target stimuli.

Internal consistency for all these subtests lies between 0.60 and 0.83 [68].

##### Seasonal pattern assessment questionnaire

The Seasonal Pattern Assessment Questionnaire (SPAQ) is a questionnaire for retrospectively assessing change in mood and vegetative functions with the seasons [69]. It is a frequently used screening instrument for assessing symptoms of SAD, with a high internal consistency [70] and has recently been used in young adults [71]. In the present study it will be administered to calculate a total seasonality score, with seasonality being the degree to which seasonal changes affect criteria such as mood, energy, sleep length, appetite, food preference, or the wish to socialize with other people [69], and thus will be used to control for seasonal effects.

##### Therapy expectancy

Therapy expectancy will be assessed by using a modification of the Credibility/Expectancy Questionnaire, which is a quick and easily administered scale for measuring treatment expectancy and rationale credibility for use in clinical outcome studies [72]. High internal consistency has been reported, lying between 0.84 and 0.85 for the whole scale. Inter-item correlations between studies ranged from 0.53 to 0.85 for the items on the expectancy factor, and between 0.62 and 0.78 for items on the credibility factor. Test-retest reliability over a 1-week period was also found to be good, at 0.82 for expectancy and 0.75 for credibility [72]. In the proposed study, the questionnaire will be used to control for placebo effects, which are expected to be relatively high for light- therapy studies.

##### Culture fair intelligence test 20 – revised

The Culture Fair Intelligence Test 20 – Revised (CFT20-R) is an economic, computerized general intelligence screening test assessing ‘general fluid ability’ [73], that is, the ability to solve formal logic tasks with varying complexity within a specific time frame. The CFT20-R uses language-free tasks and is therefore also appropriate for people with language deficiencies. It is standardized for children and adults (8.5 years of age and above) and has high test-retest coefficients (r = 0.80 to 0.83, uncorrected) and high internal consistency (α = 0.95).

##### Adverse events

At each assessment, the participants will be asked to report any adverse events (AEs). Reported AEs of light therapy side effects include jumpiness, jitteriness, headache, or nausea (for an overview, see Terman *et al*. [22]). AEs will be assessed by using open questions, asking about general AEs and their severity during the study period.

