#### Time points of assessments

The assessment time points are as follows.

•T1: The initial assessment for eligible patients will be carried out after about 1 week of care in the unit. At this point, patients will have become used to being in the hospital, and will probably have a more regular day and night rhythm.

•T2: After 2 weeks of morning light-therapy intervention, there will be a comprehensive post-therapy assessment.

•T3: One week later, depression severity will be assessed to monitor changes.

•T4: Another week later, there will be another assessment of depression severity.

•T5: Three weeks after the light-therapy interventions have ended, another comprehensive assessment will be carried out.

An overview of the timeline of the study is shown in Figure 2.

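### No adverse-event enquiry is described between T1 and T2, and no prompts for the side effects the article names, so harms of the two treatment weeks may be under-reported

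*Protocol article*

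**What the plan says.** The Adverse events section of the protocol article sets both the timing and the method of harms collection.

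- **Timing:** "At each assessment, the participants will be asked to report any adverse events".
- **Method:** "AEs will be assessed by using open questions, asking about general AEs and their severity during the study period".
- **Known effects:** the same section notes that "Reported AEs of light therapy side effects include jumpiness, jitteriness, headache, or nausea".

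The section Time points of assessments lists five assessments. The first comes before treatment: "T1: The initial assessment for eligible patients will be carried out after about 1 week of care in the unit". The next follows treatment: "T2: After 2 weeks of morning light-therapy intervention, there will be a comprehensive post-therapy assessment". T3, T4 and T5 come one, two and three weeks after the light therapy has ended.

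Three other places bear on the point. The Abstract gives the exposure as 10 sessions of 45 minutes over 2 weeks. The Control group section removes from the study any patient who misses more than two sessions. The Discussion names feasibility and acceptance of the intervention among the things this pilot is to evaluate.

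**The concern.** The first enquiry about harms after exposure begins comes when exposure is already over. A headache or a spell of jitteriness after one of the first sessions has to be remembered for up to two weeks. The patient must also decide, without a prompt, that it counts as an adverse event. Effects that are mild, brief and early are the ones most likely to be lost.

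The four effects the article expects are also non-specific. Adolescent inpatients with depression may have headaches or feel jittery before any light is given. Without a graded level at T1 for each effect, a symptom mentioned at T2 is hard to separate from one that was already there.

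The rule on missed sessions could make this worse. If exclusion also ends assessment, a patient who stops attending because of side effects would not be asked at T2, and those reports would be the most informative ones. The article does not say whether assessment continues after exclusion.

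The primary BDI-II result is not affected. What is at stake is the tolerability record of a pilot in an age group for which the article itself reports very few earlier studies, and tolerability bears on acceptance.

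**Working it through.** The article states no figure for adverse events, so there is none to reproduce. The check is first a reading of the schedule, then an illustration.

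**1. Enquiries set against exposure**

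| Assessment | Position relative to treatment | Can it pick up treatment-period events? |
|---|---|---|
| T1 | before | no |
| (none listed) | during the 2 weeks, 10 sessions | – |
| T2 | after the 2 weeks | yes, recall of up to 2 weeks |
| T3 | 1 week after treatment | yes, recall of 1 to 3 weeks |
| T4 | 2 weeks after treatment | yes, recall of 2 to 4 weeks |
| T5 | 3 weeks after treatment | yes, recall of 3 to 5 weeks |

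The open question covers the whole study period ("asking about general AEs and their severity during the study period"), not just the interval since the last visit. T2 is therefore the first and nearest recall of the treatment weeks, and three later ones follow. None is made during exposure.

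**2. Method set against expected effects**

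Four effects are named and none is stated to be prompted. The described method is the open question alone.

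**3. What incomplete capture would do**

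Inputs from the article: 60 patients, half to each arm, so about n = 30 per arm. Inputs that are assumptions: the true proportion p with a given effect, and the capture c, meaning the share of affected patients who report it when asked openly afterwards.

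- Expected number recorded in one arm = n × p × c
- Chance of recording at least one = 1 − (1 − p × c)^n

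With n = 30 and p = 0.10:

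| c | Expected recorded | Chance of at least one |
|---|---|---|
| 1.0 | 30 × 0.10 = 3.0 | 1 − 0.90^30 = 0.96 |
| 0.8 | 30 × 0.08 = 2.4 | 1 − 0.92^30 = 0.92 |
| 0.6 | 30 × 0.06 = 1.8 | 1 − 0.94^30 = 0.84 |
| 0.4 | 30 × 0.04 = 1.2 | 1 − 0.96^30 = 0.71 |

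With p = 0.20 the expected number falls from 6.0 to 4.8, 3.6 and 2.4 for the same values of c.

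These figures show only how sensitive small counts are. With about 30 patients per arm, losing one or two reports changes the picture noticeably. They do not estimate what this trial would lose.

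**The case against.** The strongest reply has five parts.

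*T2 is not the only recall.* A reader might infer that everything about the treatment weeks rests on a single recall at T2. The text does not support that: T3 to T5 also ask, and the question spans the study period. This stands. The later recalls are more distant, however, so they do not replace an enquiry during treatment.

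*An under-count is not shown.* A reader might conclude that harms are certain to be under-counted. No event rate or capture rate is given, so only a risk of unknown size can be claimed. This stands too. Nor would it help to point out that 0 events in 30 leaves an upper 95% limit of 11.6% (1 − 0.025^(1/30)). That limit follows from the sample size and would be the same with a perfect checklist.

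*Silence in a condensed article.* The patients are inpatients under continuous care. The schedule figure is not shown, and a fuller protocol may provide for spontaneous reports on the ward. It would be wrong to infer that events at sessions go unrecorded. The article is not silent on the trial's own enquiry, though: it fixes when and how patients are asked, and that stated method can be assessed.

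*Open questioning is legitimate, and both arms are asked alike.* Both are true, and no bias between the arms is demonstrated. Adverse events are not listed among the endpoints, and the article announces no comparison of side effects between arms. Equal treatment of the arms still does not protect the recorded rates from being too low.

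*Prompting has a price.* The primary outcome is self-reported. Both groups are told that two types of light therapy are being compared, and the Discussion worries that 100 lux patients may guess their allocation. A symptom list at all ten sessions could suggest symptoms and help patients work out their group. This stands and limits how often the checklist should be used.

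**Conclusion.** The point holds as a cheap improvement, not as an error in the plan. The article describes no adverse-event enquiry between T1 and T2 and no prompt for the four effects it names. Harms of the two treatment weeks therefore rest on retrospective open recall from T2 onward and may be under-reported. Patients excluded for missed sessions may not be asked at all, if exclusion ends their assessment.

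The amount of under-reporting cannot be derived from the document. The illustrative counts rest on assumed event and capture rates and on 30 patients per arm. The conclusion also assumes that no enquiry during treatment is laid down in the schedule figure or in a fuller protocol. If one is, the Adverse events section only needs to say so.

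**What to change.** Amend the Adverse events section as follows.

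- Keep the open question at every assessment.
- Add one short checklist of the four named effects, each with a severity grade, identical in both arms. Patients complete it themselves, because the investigator who delivers the treatment knows the allocation.
- Give it at T1 as the reference level, once during treatment (for example at the end of the first treatment week), and at T2, T3, T4 and T5.
- Also give it at the time of exclusion to any patient who stops early.
- Report each effect by arm, relative to its T1 level.

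This means one form and six scheduled completions per patient. Five fall at existing assessments and one can be attached to an existing session, so no extra visit is needed. The light therapy and the endpoints do not change.

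The downside is that more mild events will be recorded in both arms. There is also a small risk that prompting suggests symptoms or hints at allocation, which is the reason for asking once during treatment and not at each of the ten sessions.

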#### Time points of assessments

The assessment time points are as follows.

•T1: The initial assessment for eligible patients will be carried out after about 1 week of care in the unit. At this point, patients will have become used to being in the hospital, and will probably have a more regular day and night rhythm.

•T2: After 2 weeks of morning light-therapy intervention, there will be a comprehensive post-therapy assessment.

•T3: One week later, depression severity will be assessed to monitor changes.

•T4: Another week later, there will be another assessment of depression severity.

•T5: Three weeks after the light-therapy interventions have ended, another comprehensive assessment will be carried out.

An overview of the timeline of the study is shown in Figure 2.

**Figure 2 F2:**
[figure not shown]
**Time schedule for the pilot study.** BDI-II, Beck Depression Inventory-II; CFT 20-R, Culture Fair Intelligence Test – Revised, CGI-S/ I, Clinical Global Impression Scale-Severity/ Improvement; DLMO, Dim Light Melatonin Onset; MEQ, Morningness-Eveningness-Questionnaire; SDQ, Strengths and Difficulties Questionnaire; SF B/R, Sleep Questionnaire B - Revised; SPAQ, Seasonal Pattern Assessment Questionnaire; TAP, Tests of Attentional Performance.

### Data analysis

#### Sample-size calculation

Estimates of a clinically relevant effect size were derived from a meta-analysis that evaluated effects of bright-light therapy for seasonal and non-seasonal depression in adult outpatients [74]. A similar study for adolescent inpatients is not available. Therefore, effect-size calculation will be based on evidence from adult outpatients. Although research is generally scarce, it is assumed that the active light therapy intervention for SAD will have an effect size (pre-post) of about 0.78 [75], which can be considered a conservative estimate because effect sizes might be considerably higher [74]. Golden *et al*. [74] divided the studies used in their meta-analysis into four categories, and derived effect sizes for them. In the category ‘non-seasonal depression’, an effect size of 0.53 was reported for bright-light treatment, with a 95% confidence interval of 0.18 to 0.89. Conservative calculations indicate that the expected outcome for our study will require a total sample size of 54 subjects (α = 0.05, two-sided test) to achieve a power of 80%.

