#### Control group

A valid placebo group will be created by randomly assigning half of the patients to the control group to receive 2 weeks of inactive light therapy not exceeding 100 lux at eye level in gaze direction (Luxor LED light alarm clock, lowest level; DAVITA^®^ Medizinische Produkte GmbH & Co. KG, Kleve, Germany), with each session lasting for 45 minutes. Each session will commence about 7.5 h after the estimated DLMO to parallel the experimental group.

Finding an appropriate control group for light therapy to minimize placebo effects is difficult, because these effects are expected to be relatively high [19,45,46]. To design conditions that the patients will not consider a control group, we have chosen professional light-therapy devices for both groups, adjusting the lux levels respectively. To control for possible expectation bias, both groups will be instructed that the aim of the study is to compare two different types of light therapy. Moreover, to minimize bias, the therapists on the respective units will be informed that the light therapy for both groups is active.

To ensure that an appropriate and constant number of lux is administered in each group, intensities will be quantified using a lux meter (PCE-172; PCE Instruments, Meschede, Germany). The light intensity that will be used in this study lies within the range of normal daylight exposure. Its long-term ocular safety has been shown in patients with SAD who received bright-light therapy at an illuminance level of 10,000 lux [47].

During the interventions, patients will be allowed to have breakfast or read magazines and books with neutral content (for example, magazines containing plain information without emotionally arousing material). To ensure that every participant has received the same amount of light therapy at the end of the treatment period, treatment can be prolonged for up to 1 day if a patient misses a light-therapy session for some reason (for example, somatic illness). If a patient misses more than two sessions, he/she will be excluded from the study. In total, about three patients can be treated in parallel within each group (see Figure 1 for a flow chart of the study).

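### The claim of 80% power with 54 patients appears to rest on 0.78, a figure labelled pre-post and for seasonal depression; the same calculation at the paragraph's own non-seasonal figure of 0.53 gives 48%

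*Protocol article*

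**What the plan says.** The Sample-size calculation section of the protocol article gives two effect sizes. For seasonal affective disorder (SAD), "it is assumed that the active light therapy intervention for SAD will have an effect size (pre-post) of about 0.78 [75"]. The authors call this value conservative, on the ground that the true effect may be larger. For the meta-analysis category of non-seasonal depression, "an effect size of 0.53 was reported for bright-light treatment, with a 95% confidence interval of 0.18 to 0.89". The section then concludes: "Conservative calculations indicate that the expected outcome for our study will require a total sample size of 54 subjects", at two-sided alpha 0.05 and 80% power. It does not say which effect size, test or correlation produced 54.

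Other sections fix what has to be powered:

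- The Control group section allocates 1:1 ("randomly assigning half of the patients to the control group") between 10,000 lux and at most 100 lux. It says that minimising placebo effects is difficult "because these effects are expected to be relatively high".
- The Statistical analyses section plans a repeated-measures ANCOVA of BDI-II from T1 to T5, with group as the between-patient factor and baseline BDI-II controlled.
- Eligibility requires moderate to severe depression, not SAD. The Discussion frames the question as one about non-seasonal symptoms in young people.
- Planned enrolment is 60.

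**The concern.** The power statement should describe the randomised contrast. A pre-post effect in the active arm is the sum of the specific effect of light, the placebo response, spontaneous change and the effect of the usual inpatient care that both arms receive. Whatever improvement the control arm shows must be subtracted before the figure describes active minus control. If 0.78 is what its label says, using it as a between-group difference overstates the power.

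The population differs as well. The 0.78 is for SAD, whereas the category closest to this trial has the lower 0.53. Describing the calculation as conservative is hard to defend if it used the larger of the two quoted values.

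At stake is how a non-significant result is read. Someone who trusts the 80% could take it as evidence against a useful effect that the calculation behind 54 would miss about half the time.

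**Working it through.** **Inputs from the protocol.** Two-sided alpha 0.05, power 80%, 1:1 allocation, 54 in total (27 per arm), planned 60 (30 per arm); effect sizes 0.78 and 0.53 (95% CI 0.18 to 0.89).

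**Step 1: reproduce 54.** The normal approximation is n per arm = 2(1.960 + 0.842)²/d². At d = 0.78 this is 15.70/0.608 = 25.8, so 26 per arm (52 in total). The exact t-test needs 26.8, so 27 per arm and 54 in total, with power 80.3%. Solving back from 27 per arm gives d = 0.777. Other standard readings that add no correlation miss 54:

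- two-sample at 0.53: 114 two-sided, 90 one-sided;
- two-sample at 0.78, one-sided: 44;
- paired pre-post test: 15 patients at 0.78, 30 at 0.53.

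**Step 2: the same calculation at 0.53**, assuming that this is a between-group difference. The non-centrality is d√(n/2).

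- 27 per arm: 0.53 × √13.5 = 1.95, power 48.1%.
- 30 per arm: 0.53 × √15 = 2.05, power 52.3%.
- 80% power needs 56.9, so 57 per arm and 114 in total.
- Across the quoted interval with 54 patients, power runs from about 10% (d = 0.18) to about 89% (d = 0.89).

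**Step 3: how far the planned analysis could change this.** The protocol gives no correlation, so r below is an assumed range, with equal correlation between all visits. In each case the effective difference goes into the same t-test.

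- One post-treatment visit, baseline-adjusted: d/√(1 − r²).
- Mean of T2 to T5, baseline-adjusted, constant effect of 0.53: d/√v, with v = (1 + 3r)/4 − r², which is 0.385, 0.375 and 0.285 at r = 0.3, 0.5 and 0.7.
- The same mean with an illustrative effect fading over T2 to T5 (0.53, 0.40, 0.30, 0.20): average 1.43/4 = 0.3575, divided by √v.

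| Power with 54 / 60 patients | r = 0.3 | r = 0.5 | r = 0.7 |
|---|---|---|---|
| One visit, adjusted | 51.7 / 56.2% | 59.8 / 64.5% | 76.3 / 80.7% |
| Mean of T2–T5, constant effect | 86.9 / 90.2% | 87.7 / 90.9% | 94.7 / 96.6% |
| Mean of T2–T5, fading effect | 54.7 / 59.3% | 55.8 / 60.4% | 67.5 / 72.3% |

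With one visit and 54 patients, 80% is reached only at r of about 0.73. With a constant effect averaged over four visits, it is passed at every r shown.

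**The case against.** The best defence is that an unadjusted t-test is not the planned analysis. Averaging four post-baseline visits with baseline adjustment could give more than 80% power at 0.53 with 54 patients. The figure of 54 can even be approached from 0.53: at a correlation of 0.3, the unadjusted mean of four post-baseline visits needs 56 patients and the mean of five visits needs 52. The input of 0.78 is therefore a strong inference, not a documented fact. The exact match without any unstated parameter favours it but does not prove it.

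This part of the defence stands. A reader might infer that the trial has about 50% power, or that only a baseline correlation near 0.7 could bring 60 patients to 80%. The protocol supports neither as a statement about the planned model; both describe a comparison at a single visit. Equally, the protocol cannot claim the gain from averaging. It states no correlations, and T3 to T5 fall after light therapy has ended, so a constant effect cannot be presumed.

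Two further points have some force. The cited sources are not available here, so the nature of 0.78 and 0.53 rests on the text: the pre-post label may be loose, and 0.53 as a between-group contrast is an assumption. Also, the first use of conservative refers to SAD and 0.53 to a different category, so the two are not in literal contradiction. What remains is that the label carries over to the 54 for this trial, with no stated basis.

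The pilot label and the planned 95% confidence intervals soften the consequences. They do not excuse the figure, because the article claims 80% power and plans significance testing at 0.05.

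**Conclusion.** The power statement is not supported as written. Its inputs and test are unnamed. The one simple calculation that reproduces it exactly uses a value the text itself labels pre-post and seasonal, in a trial that compares randomised groups and asks about non-seasonal depression. On that calculation, the protocol's own non-seasonal figure gives 48% power with 54 patients and 52% with 60, against the 80% claimed.

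This rests on three assumptions: that 0.78 was the input (inferred), that 0.53 is between-group (not stated), and that the comparison is unadjusted at a single visit. Under the planned repeated-measures model at 0.53 with 54 patients, power could be about 87% or more if the effect is constant, or about 55 to 68% under the illustrative fading effect, at the correlations tabulated. The documents do not allow a choice between these. The finding is therefore that the 80% claim lacks a valid stated basis, not that the trial's true power is known to be about 50%.

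**What to change.** Keep the planned 60 patients and reword the sample-size paragraph:

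- State that 54 evaluable patients (27 per arm) give 80% power, at two-sided alpha 0.05, for a between-group standardised difference of 0.78 in an unadjusted two-group comparison.
- Remove the description as conservative, and remove the pre-post SAD effect as the basis.
- Report that for a between-group difference of 0.53 the same unadjusted single-visit calculation gives about 50% power (48% with 54, 52% with 60). Say whether the cited 0.53 is in fact a between-group effect.
- Claim higher power only together with the repeated-measures model, the assumed correlations and the assumed persistence of effect over T2 to T5. If 54 was in fact derived that way, give those inputs.
- State that a non-significant result will be interpreted through the 95% confidence interval of the between-group difference.

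The cost is one rewritten paragraph and a less favourable stated power. The number of patients, the endpoint and the analysis do not change.
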